#### Safety device acquisition and use

Participants will be asked whether they have any of the 22 possible types of safety devices installed in their homes, e.g., fire escape ladder, medicine lock box, etc. Response choices will include the following options: *yes, no, not sure, and not applicable.* Participants who report *no* to one or more safety devices will be asked whether they intend to purchase and install these devices in the future *(yes, no, not sure).*

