The aim of the study described in this protocol is to evaluate the impact of and determine whether a mobile technology-based health behavior change intervention, the *Make Safe Happen®* app, is effective in increasing (1) safety knowledge; (2) safety actions/behaviors; and (3) safety device acquisition and use; and (4) behavioral intention (planning to take safety actions or acquire devices) for the prevention of unintentional home-related injuries, compared with no intervention.

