## Results and discussion

### Outcomes and measures

Primary outcomes will include: (1) safety knowledge; (2) safety behaviors; (3) device acquisition and use; and (4) behavioral intention to take safety actions. Participants will self-report these at baseline (pretest) and at follow-up (posttest). A combination of yes-no, multiple choice and Likert scale response options will be used. A sample of questions from the pretest and posttest surveys will be vetted for coherent meaning and level of difficulty via an hour-long cognitive interview with 20 parents prior to the launch of the study. A pilot study with 200 participants will be completed prior to the study launch to examine the distribution of participants’ responses and to address any technical difficulties with the pretest survey instrument.

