### Data analysis plan

Data analysis will be primarily comprised of two activities: 1) the generation of descriptive information summarizing the sample and its characteristics; and 2) the analyses related to the aims and hypotheses. The central hypothesis is that parents in the IG will have higher safety knowledge, do more safety behaviors, have increased behavioral intention to take safety actions, and be more likely to acquire and use safety devices posttest, as compared to the CG. Linear mixed model regression will be used to analyze safety knowledge outcome and longitudinal logistic regression models will be run for behavioral intention and safety actions. Primary outcomes for the safety behaviors and device use will be assessed while stratifying on the index child age group. Analyses will be undertaken to examine the hypotheses that the IG will have higher change at posttest from baseline in safety knowledge, safety behaviors, behavioral intention, safety device use and acquisition than the CG.

Besides the intent-to-treat analyses of safety knowledge, safety behaviors and behavioral intention, safety device use and acquisition, we will also conduct exposure analyses to examine the relationship between outcomes and exposure to the intervention. For the IG participants those who enter a participant ID in the *Make Safe Happen®* app will be asked to complete a posttest survey. For the CG participants, those who complete the pretest survey will be asked to complete a posttest survey since we cannot confirm download and use of the control condition app. We plan to link app analytics for IG participants to their pretest and posttest survey responses, for example, if a participant uses the *Make Safe Happen®* app to add the poison control center emergency number to their contacts we will check to see whether that participant got the poison control center emergency number safety knowledge question correct in the pre- and posttest surveys. All study data will be stored on password protected computers of the study personnel. The study will be monitored by the study investigators.

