The pretest and posttest survey data will be limited due to the nature of self-reported data and may also be subject to reporting bias. Further, the surveys will be conducted close together in time (a span of 7–10 days apart) therefore we may see a learning effect of having recently taken the survey. A follow-up period of 7 to 10 days was used in order to allow recruited participants time to download and use the app. We do not expect that participants will complete all of the recommended safety actions or safety device installations in this limited time period. We opted to keep the follow-up period relatively short in an effort to prevent loss to follow-up. While we will have actual app data to report on what users completed within the app, at best these data will be a proxy for real behaviors or safety actions. Further, the requirement for a smartphone Internet connection in order to transmit the data from the *Make Safe Happen®* app to the online platform that stores these data as well as the app data processing latency of 24—48 h may both cause delays in distribution of posttest surveys to IG participants. An additional limitation is that we will not be able to confirm or track the CG recipe app usage.

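### Device acquisition is part of a primary outcome, but the device item as described records only installed devices, so purchases not yet fitted at 7–10 days are missed.

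*Protocol article*

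**What the plan says.** Under Outcomes and measures, the primary outcomes include "3) device acquisition and use; and (4) behavioral intention to take safety actions". They are self-reported at pretest and posttest. The hypothesis under Data analysis plan is that intervention parents will "be more likely to acquire and use safety devices posttest, as compared to the CG". The aim at the end of the Background defines the intention outcome as "behavioral intention (planning to take safety actions or acquire devices"), so intention covers devices as well as actions.

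The measure is described under Safety device acquisition and use: "Participants will be asked whether they have any of the 22 possible types of safety devices installed in their homes". The responses are yes, no, not sure and not applicable. Participants who answer no "will be asked whether they intend to purchase and install these devices in the future".

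The Discussion puts the two surveys 7–10 days apart and adds: "We do not expect that participants will complete all of the recommended safety actions or safety device installations in this limited time period".

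**The concern.** Acquiring a device and installing it are two steps, and the second can lag the first. The app is built to act on the first: Intervention and control group content describes links to an online seller and a shopping list, and says that purchase had been identified as a barrier. An order or a purchase must come before installation, so it is the step more likely to be complete after a week or so. The item as described looks only at the later step.

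Two things are at stake. The acquisition half of the third primary outcome has no measure of its own, so a real effect on purchasing may be understated. And a parent who has bought a device but answers no is asked about planning to buy it, so a completed purchase can enter the fourth primary outcome as intention.

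**Working it through.** The plan states no figure on this point, so there is none to reproduce. The check is first a reading of the item against the outcome, then an illustration on assumed rates.

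**Outcome against item**

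| State of a device at posttest | Acquired? | In use? | Literal answer to the item | Asked about intention? |
|---|---|---|---|---|
| Installed | yes | yes | yes | no |
| Bought or ordered, not fitted | yes | no | no (possibly not sure) | yes, if the answer is no |
| Neither | no | no | no | yes |

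The second and third rows can receive the same answer and the same follow-up question. No other item described in the article separates them. The one example of a one-time action under Safety behaviors and behavioral intentions, a carbon monoxide detector, also joins buying with installing. App records cannot fill the gap: they are linked to surveys for the intervention group only, so they give no between-arm contrast.

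**Size of the attenuation**

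Let a0 and a1 be the new-acquisition proportions in the control and intervention groups, and f the share of acquired devices installed by posttest, taken as equal in both arms.

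- Difference in acquisition: a1 − a0
- Difference seen by an installed-only item: f × (a1 − a0)
- Part not seen: (1 − f) × (a1 − a0)

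Inputs from Sample size: a posttest sample of 1200 at 5:1, so 1200 × 5/6 = 1000 intervention and 1200 × 1/6 = 200 control. Assumed, because the article gives none: a0 = 5%, a1 = 12%, the values of f, and a two-sided 5% test for one device.

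Power = Φ[(|p1 − p0| − 1.96 × SE0) / SE1], where p0 = f × a0, p1 = f × a1, SE0 uses the pooled proportion and SE1 the separate proportions.

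- f = 1: 5% v 12%, pooled 10.83%, SE0 = 0.02407, SE1 = 0.01852. (0.07 − 1.96 × 0.02407)/0.01852 = 1.23, power 89%.
- f = 0.5: 2.5% v 6%, pooled 5.42%, SE0 = 0.01753, SE1 = 0.01335. (0.035 − 1.96 × 0.01753)/0.01335 = 0.05, power 52%.

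| Share installed by posttest (f) | Measured difference, 5% v 12% | Power, 5% v 12% | Power, 10% v 20% |
|---|---|---|---|
| 100% (same as recording acquisition) | 7.0 points | 89% | 95% |
| 90% | 6.3 points | 85% | 92% |
| 75% | 5.25 points | 75% | 85% |
| 50% | 3.5 points | 52% | 63% |
| 25% | 1.75 points | 23% | 30% |

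At f = 50% and 5% v 12%, the unseen 3.5 points are a net excess of intervention parents who have bought the device but may be sent to the intention question.

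**Sensitivity**

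- Test formula: with unpooled variance throughout, 5% v 12% gives 97% at f = 100% and 75% at f = 50%.
- Sample size: the 1200 does not follow from the article's own inputs, since 5000 × (1 − 0.40) = 3000. With 2500 v 500, power at f = 50% is 94% for 5% v 12% and 97% for 10% v 20%.

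The loss of power depends on these choices. The shrinkage of the measured difference by the factor f does not.

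**The case against.** **The questionnaire is not shown.** The article paraphrases the device item, and the section on behaviors announces 31 questions but accounts for 14 + 15 = 29. A purchase item cannot be ruled out. This stands as a limit: the point concerns the measure as described. But the article is not silent here; it gives the question, the response options and the routing for this primary outcome.

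**Not every purchaser answers no.** A reader might infer that anyone with an unfitted device must answer no and is scored as not having acquired it. The article does not support that. Not sure is also offered and is not described as leading to the intention question, and no scoring rule is given. The two devices named as examples, a fire escape ladder and a medicine lock box, may count as in place once they are in the home. The problem is confined to devices that need fitting or have not arrived, and the article does not say how many of the 22 these are.

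**Acquisition and intention remain distinct.** A reader might also infer that the third and fourth primary outcomes can no longer be told apart. They can: installed status and intention are separate responses, and nobody counts under both for the same device. A purchaser adds to intention only by answering yes to a question on purchasing and installing, which fits poorly once the purchase is made; and that parent does still intend to install. Some misclassification is possible, and its size is unknown.

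**Installation is the outcome that matters.** An unfitted device does not yet protect a child, and the error described is conservative for the device outcome. That is a sound reason to analyze installed devices, but not to report the result as acquisition. The short window is a reasoned trade-off and is not challenged here.

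**Conclusion.** The point holds for the item as the article describes it. Acquisition is named in a primary outcome and in the central hypothesis, yet the item records installation only, at a time when the authors expect installation to be incomplete. For devices that need fitting, the acquisition contrast is biased towards zero by the share not yet installed, and some purchases may appear as intention.

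The article allows no estimate of the size. In the 5% v 12% illustration at 1000 v 200, power runs from 89% with acquisition recorded to 85%, 75%, 52% and 23% as the installed share falls from 90% to 25%. This rests on assumed rates, an installed share equal in both arms, a single-device comparison that ignores the planned pretest–posttest modelling, and a posttest total that the article's own arithmetic does not support. With a larger sample the loss of power is much smaller; the mismatch between outcome and item remains.

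**What to change.** Keep the 7–10 day window. At both pretest and posttest, split the yes response for each device into two levels: *have it and it is installed*, and *bought or ordered, not yet installed*. Score acquisition as either level and use as the first only. Ask purchase intention only of parents with neither.

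The cost is one added response option in an online survey, a slightly longer item, and two device scores to define and report where there was one.

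If the survey can no longer be changed, rename the outcome *installed devices* and drop the separate claim about acquisition. That costs nothing in data collection, but gives up any conclusion on the purchasing step that the app is designed to ease.

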### Data analysis plan

Data analysis will be primarily comprised of two activities: 1) the generation of descriptive information summarizing the sample and its characteristics; and 2) the analyses related to the aims and hypotheses. The central hypothesis is that parents in the IG will have higher safety knowledge, do more safety behaviors, have increased behavioral intention to take safety actions, and be more likely to acquire and use safety devices posttest, as compared to the CG. Linear mixed model regression will be used to analyze safety knowledge outcome and longitudinal logistic regression models will be run for behavioral intention and safety actions. Primary outcomes for the safety behaviors and device use will be assessed while stratifying on the index child age group. Analyses will be undertaken to examine the hypotheses that the IG will have higher change at posttest from baseline in safety knowledge, safety behaviors, behavioral intention, safety device use and acquisition than the CG.

Besides the intent-to-treat analyses of safety knowledge, safety behaviors and behavioral intention, safety device use and acquisition, we will also conduct exposure analyses to examine the relationship between outcomes and exposure to the intervention. For the IG participants those who enter a participant ID in the *Make Safe Happen®* app will be asked to complete a posttest survey. For the CG participants, those who complete the pretest survey will be asked to complete a posttest survey since we cannot confirm download and use of the control condition app. We plan to link app analytics for IG participants to their pretest and posttest survey responses, for example, if a participant uses the *Make Safe Happen®* app to add the poison control center emergency number to their contacts we will check to see whether that participant got the poison control center emergency number safety knowledge question correct in the pre- and posttest surveys. All study data will be stored on password protected computers of the study personnel. The study will be monitored by the study investigators.

### Sample size

We plan to enroll 5000 participants, and we estimate a 40% loss-to-follow-up, which will provide us with the needed sample size of 1200 in the posttest sample for the planned analyses. A power analysis indicated it would not be necessary to have equal numbers of participants assigned to the IG and the CG. Therefore, participants will be randomized to the treatment groups using a 5:1 ratio, allowing efficient allocation of participants to the IG or CG (respectively) within the online survey group. Focus group participants and home visit participants will not be randomized, although all focus group and home visit participants will receive the Make Safe Happen app intervention. The randomization will be completed by the use of a computer program embedded within the online survey, which randomly generates a number between 1 and 120 for each participant. Numbers between 1 and 100 will be assigned to the IG, while numbers between 101 and 120 will be assigned to the CG. Our proposed sample size reflects consideration of our proposed attrition rate and is based on previous research using online survey panels. Additionally, we will aim to recruit a diverse sample of parents ≥18 years old based on sex (30% male, 70% female), ethnicity (maximum of 66% White, non-Hispanic), and age of index child (~ 20% in each of the five age brackets).

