## Methods

### Study design and setting

The *Make Safe Happen®* app (Additional file 1) evaluation study will be a two-group, randomized controlled trial with pre- and posttest elements (no blinding), and will involve 1200 parents of children aged 0–12 years. These data will be collected in the U.S. The intervention group (IG) will use the *Make Safe Happen*® app and receive information about the prevention of unintentional child home-related injuries. The “attention-matched” control group (CG) will use an app to receive information about dinner recipes. Surveys measuring safety knowledge, behaviors and behavioral intentions, and safety device acquisition and use will be administered before and after app use (Fig. 1). This study was approved by the Institutional Review Board (IRB) at Nationwide Children’s Hospital. Plans for protocol modifications or for communications to relevant parties will be made to the study investigators, IRB, trial participants if necessary. Study investigators will have access to the final dataset. See Standard Protocol Items: Recommendations for Interventional Trials (SPIRIT) Checklist (Research Checklist) (Additional file 2).

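### Enrolling 5000 with 40% loss leaves 3000 at posttest, not the stated 1200: the enrolment, the loss rate or the posttest target must be wrong

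*Protocol article*

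**What the plan says.** The Sample size section of the protocol article links three figures in one sentence: "We plan to enroll 5000 participants, and we estimate a 40% loss-to-follow-up, which will provide us with the needed sample size of 1200". The sentence goes on to place the 1200 at posttest: "the needed sample size of 1200 in the posttest sample for the planned analyses". The same section gives the allocation, "participants will be randomized to the treatment groups using a 5:1 ratio", and explains where the total comes from: "Our proposed sample size reflects consideration of our proposed attrition rate and is based on previous research using online survey panels".

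The section Study design and setting gives a total as well, saying that the trial "will involve 1200 parents of children aged 0–12 years". It does not say whether this number is enrolled or analysed.

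Two other rules remove participants, and neither has a rate attached. Under Screening, enrollment and randomization, unusually fast responders are disqualified and left out of the analyses. Intervention group (IG) parents who do not download the app or enter their ID cannot take the posttest. The Data analysis plan repeats the ID condition for the IG and invites every control group (CG) parent who completed the pretest.

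**The concern.** Enrolment, loss and posttest size are tied by one multiplication, so any two of them fix the third. Here all three are printed and they disagree by far more than rounding. A reader cannot tell how many parents will be recruited, how large each arm will be at posttest, or which retention rate the trial should be judged against.

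The loss rate matters beyond the head count. The article promises intent-to-treat analyses, yet only IG parents must clear the download-and-ID step before the posttest. Loss is therefore likely to be heavier in the IG, and a comparison among completers is much harder to trust at 76% total loss than at 40%. A single rate for both arms hides this.

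**Working it through.** **Inputs.** Enrolment N = 5000, loss d = 40%, posttest target T = 1200 and allocation 5:1, all from Sample size. The figure 1200 also appears in Study design and setting.

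**Attempt to reproduce 1200.**

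| Calculation | Result |
|---|---|
| N(1 − d) = 5000 × 0.60 | 3000 |
| N·d = 5000 × 0.40 | 2000 |
| N/(1 + d) = 5000/1.40 | 3571 |
| N(1 − d)² | 1800 |
| N(1 − d)³ | 1080 |
| IG only, 5000 × 5/6 × 0.60 | 2500 |
| CG only, 5000 × 1/6 × 0.60 | 500 |
| N·d·(1 − d) = 5000 × 0.40 × 0.60 | 1200 |

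The first line is the calculation that the sentence describes, and it gives 3000. Only the last line gives 1200. It needs a first stage at which just 40% of enrolled parents go on, followed by 40% loss among those, and the article states no such stage.

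**Working backwards.**

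- Enrolment needed for 1200 at 40% loss: 1200/(1 − 0.40) = 2000. The common slip of multiplying, 1200 × 1.40 = 1680, does not give 5000 either.
- Loss implied by 5000 falling to 1200: 1 − 1200/5000 = 76%, against 40% stated.
- If the 1200 in the design section were read as enrolment, 1200 × 0.60 = 720 would remain at posttest.

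**Arm sizes at posttest, equal loss in both arms.** 3000 at 5:1 is 2500 IG and 500 CG; 1200 at 5:1 is 1000 and 200. With about one fifth of parents in each of the five child-age brackets, that is about 500/5 = 100 or 200/5 = 40 controls per bracket.

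**Detectable difference.** The article gives no power, significance level or effect size. I assume 80% power, a two-sided 5% level and a simple two-group comparison of means, so d = (1.96 + 0.84) × √(1/n₁ + 1/n₂):

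- 2500/500: 2.80 × √(1/2500 + 1/500) = 0.14 SD
- 1000/200: 2.80 × √(1/1000 + 1/200) = 0.22 SD

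**Unequal loss, as an illustration.** At 5:1, 5000 splits into about 4167 IG and 833 CG. If the CG keeps 60% (500), a total of 1200 leaves 1200 − 500 = 700 in the IG, a retention of 700/4167 = 16.8%. The detectable difference is then 2.80 × √(1/700 + 1/500) = 0.16 SD.

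**The case against.** The best defence is that nothing was miscalculated and a stage was left out. The article does describe removals that are not ordinary loss to follow-up: the IG download-and-ID condition and the exclusion of fast responders. If about 2000 of the 5000 remained eligible and 40% of those were then lost, 1200 would follow exactly. This is possible, but no such rate appears anywhere, and the ID condition applies to one arm only. If it is the explanation, total planned loss is 76% and the printed 40% misdescribes it, so the sentence still needs correcting.

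A second defence reads 1200 as a minimum, which 3000 would meet. The trial would then not be short of participants. But it would be enrolling 3000 more parents than the 2000 needed, with no reason given, although the section presents the size as already reflecting attrition.

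Three further points stand as limits on the argument:

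- The value of 720 depends on reading the design section's 1200 as enrolment. The Sample size section places 1200 at posttest, so loose wording in the design section is the likelier explanation.
- The 0.22 SD assumes equal loss in the two arms. With loss concentrated in the IG, the figure could be nearer 0.16 SD.
- The planned analyses are mixed and longitudinal logistic models, so the SD figures show scale only.

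**Conclusion.** The concern holds. As written, 5000 enrolled and 40% loss give 3000 at posttest. Either the posttest size is off by a factor of 2.5, or the total loss is understated by 36 percentage points (76% against 40%), or the enrolment should be 2000. This rests only on printed figures and one multiplication.

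The document does not settle which figure is wrong. Because 1200 appears in two sections, the enrolment or the loss rate is the likelier error. The arm sizes of 1000/200 and 2500/500 assume equal loss by arm, and the detectable differences also rest on my assumed power and significance level. The 1200 itself cannot be checked, because the inputs to the power analysis are not given; the finding does not depend on it.

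**What to change.** Replace the sentence with one consistent set, by arm: number randomised, expected posttest response in the IG and in the CG, and the resulting posttest number. If a download or eligibility stage was assumed, give its rate separately, so that the total loss can be read off. Two sets that would be consistent overall are 2000 randomised with 40% loss giving 1200, and 5000 randomised with 76% loss giving 1200. The authors must say which plan, or what other set, they intended. In Study design and setting, describe 1200 as the posttest target and give the number randomised beside it.

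The cost is wording only. Either the stated loss becomes less favourable or the planned enrolment falls.
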